### ***Preparation of pomegranate juice:***

Pomegranates of Iranian species (robab) will be picked by hand and stored in tanks. All fruits will be crushed with skin. The juice will be pasteurized, concentrated and filtered at a

temperature of 18 ° C. The product will be packaged in a disposable bottle and given to the patient daily. According to the manufacturer's recommendation, pomegranate juice will be stored at room temperature (25 ° C) until consumption [17].

***Preparation of placebo drink:***

Placebo is prepared by the addition of 0.02 % pomegranate emulsion of Mongolia Company to water. This protocol is approved by the Ministry of Health and is in accordance with the instructions on the product. The color is also matched to the natural pomegranate juice by edible color with the international code of E-122 [21].

**Study eligibility:**

***Inclusion criteria:***

- written informed consent form
- Age 18 years old or above
- COVID-19 diagnosis based on polymerase chain reaction (RT-PCR)
- Acceptance for random assignment
- Willingness to participate in research study

***Non-inclusion criteria***

- Pregnancy or lactation
- IgA <61 mg/dl
- Disseminated intravascular coagulation or any other types of coagulopathy
- Severe congestive heart failure
- Participate in any clinical trial within the past 30 days prior to enrollment in the present work
- Other contraindications prescribed by the specialist.

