### **Study Design & randomization:**

The present study will be performed as a Randomized, Placebo-Controlled, Double-Blind, Parallel-Group clinical trial on patients with Covid-19 admitted to Shahid Jalil Hospital in Yasuj (Kohgiluyeh & Boyr Ahmad province, south-west of Iran). The study protocol was approved by the Ethics Committee of the School of Nutrition and Public Health ( ) in Yasuj University of Medical Sciences and is in agreement with the declaration of Helsinki of the world medical association. This study was also registered in the Iranian Center for Clinical Trials ( ). Patients will be randomly divided into two groups of intervention (n=24), and placebo (n=24), by block random sampling method, which randomizes participants into 4 different blocks in each group, based on gender and age . Intervention group receive 500 ml of natural whole pomegranate juice twice a day, after lunch and dinner and control group receive the same amount of placebo with the same color and taste as natural juice. The pomegranate juice and placebo will be administered to patients by two nurses in opposite shifts. Patients will be followed for 14 days and the objectives of the study will be fully explained to the patient and their companions. An informed written consent form will be also obtained.

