### **Clinical, Para clinical and dietary intake assessments:**

A demographic questionnaire containing information about age, sex, habitat, education, occupation etc., will be taken from patients. Medical history and medications/supplements history will also be asked of the patient or his companion.

Height, weight and waist to hip ratio (WHR) will be measured by standard methods [1] as well as the body mass index (division of weight in kilograms to the height in meters squared).

For the purpose of evaluating detailed information about nutrient intake and the food pattern, a 24-hour dietary recall for 3 days (including a weekend day) will be taken by a well-trained interviewer. Dietary intakes will be entered into Nutritionist IV software for further analysis.

10 cc blood samples will be obtained after 12 hour overnight fasting to measure complete blood count (CBC) and inflammatory indices including CRP, ESR & IL-6, at the baseline and by the end of week-2. In the case of patient discharge earlier than scheduled, they will be followed up after discharge and receive pomegranate juice or placebo. The length of hospital stay, disease complications, drug and prescription dosing and mortality rate will be recorded on a daily basis. If the patient refuses to continue the study for any reason, blood sample will be drawn on the same day.

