## **Study objectives:**

### ***Primary objectives***

To assess of the effect of Punica granatum juice on inflammatory biomarkers and CBC in patients with Covid-19

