### ***Secondary objectives***

- To assess and compare the mean or median serum concentrations of interleukin 6 before and after the intervention and between the intervention group with placebo
- To assess and compare the mean or median serum concentrations of ESR before and after the intervention and between the intervention group with placebo
- To assess and compare the mean or median serum concentrations of CRP before and after the intervention and between the intervention group with placebo
- To assess and compare the mean or median of CBC parameters before and after the intervention and between the intervention group with placebo

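### Apart from coagulopathy, no eligibility item keeps out patients whose CBC, CRP, ESR or IL-6 is determined by another disease or prior treatment, which costs precision at 24 per arm

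*Protocol*

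**What the plan says.** Under Primary objectives the aim is the "effect of Punica granatum juice on inflammatory biomarkers and CBC in patients with Covid-19". The assessments section fixes the measures: blood is drawn "to measure complete blood count (CBC) and inflammatory indices including CRP, ESR & IL-6, at the baseline and by the end of week-2". Secondary objectives lists IL-6, ESR, CRP and CBC again, one by one.

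Any consenting adult with RT-PCR-confirmed COVID-19 who accepts randomisation can enter. The Non-inclusion criteria then remove pregnancy or lactation, low IgA, severe heart failure, recent trial participation, "Disseminated intravascular coagulation or any other types of coagulopathy" and "Other contraindications prescribed by the specialist". Coagulopathy is the only named item that touches blood disease.

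Allocation is 24 to 24 in blocks based on gender and age. Medical and drug history is taken, and "drug and prescription dosing and mortality rate will be recorded on a daily basis", but no listed criterion uses this information. Data analysis plans a Kolmogorov-Smirnov check, then an independent t test or Mann-Whitney test between groups and paired tests within groups.

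**The concern.** The entry criteria are not matched to the endpoints. Blood malignancy, cytotoxic chemotherapy, recent transfusion, active autoimmune or chronic inflammatory disease, and earlier treatment acting on IL-6 can each determine one or more of the primary measures, whatever the drink does. Such patients add variation unrelated to the question.

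The blocking factors are gender and age, so balance on these conditions is left to chance, and in arms of 24 chance balance is poor for a handful of patients. Eligibility is settled in the protocol. An analysis plan can adjust for these patients but cannot change who was enrolled.

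**Working it through.** **Plan's own figure.** The protocol states 48 patients, 24 per arm, without an effect size, SD or power, so that number cannot be reproduced. The check asks instead what 24 per arm can detect and how far atypical patients erode it.

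**Inputs.** From the protocol: n = 24 per arm, significance level 0.05 (two-sided assumed), t test or Mann-Whitney. Assumed: normal data for the other patients; k = 1 or 2 atypical patients; each lies m = 3, 5 or 10 SD above the rest on the scale compared.

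**Detectable difference at 80% power.** (1.960 + 0.842) × √(2/24) = 2.802 × 0.2887 = 0.81 SD.

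**Chance that such patients enter.** If a share p of eligible inpatients is affected, the chance of at least one among 48 is 1 − (1 − p)^48:
- p = 2%: 1 − 0.98^48 = 62%
- p = 5%: 1 − 0.95^48 = 91%
- p = 10%: 1 − 0.90^48 = 99%

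The protocol gives no p. These figures cover any of the conditions together and do not measure harmful imbalance.

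**Imbalance.** One such patient always sits in one arm only. Ignoring blocking, two share an arm with probability 2 × C(24,2)/C(48,2) = 552/1128 = 49%.

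**Pull on an arm mean.** k × m/24. At 5 SD, one patient gives 5/24 = 0.21 SD and two give 10/24 = 0.42 SD, about half the detectable difference. Two at 10 SD give 20/24 = 0.83 SD.

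**Power at a true effect of 0.81 SD.** Simulation, 20,000 trials per setting, atypical patients placed at random among the 48:

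| Atypical patients | Distance | t test | Mann-Whitney |
|---|---|---|---|
| none | – | 79% | 76% |
| 1 | 3 SD | 72% | 73% |
| 1 | 5 SD | 60% | 72% |
| 1 | 10 SD | 39% | 71% |
| 2 | 3 SD | 65% | 69% |
| 2 | 5 SD | 49% | 68% |
| 2 | 10 SD | 24% | 68% |

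A separate simulation of the 5 SD rows agreed to within about two points (61% and 47% with the t test, 72% and 67% with Mann-Whitney).

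**Type I error.** With random placement and no true effect, the t test rejects in 2.1% to 4.9% of trials and Mann-Whitney in 4.6% to 4.9%.

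**Does the normality check divert these cases to the rank test?** In an arm of 24 with one patient at 5 SD, Kolmogorov-Smirnov rejects in 43% of runs with the Lilliefors correction and 1% without. With two at 5 SD it rejects in 71% and 5%. At 10 SD it almost always rejects if corrected (99% or more). The protocol does not say which form is used.

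**The case against.** The strongest reply is that the planned analysis already limits the damage. A grossly abnormal value fails the normality check and goes to a rank test. Take one white cell count of 100 against a typical 7 ×10⁹/L (illustrative values): the arm mean moves (100 − 7)/24 = 3.9 ×10⁹/L. When this case was simulated with an SD of 2, 3 or 4 (assumed), normality was rejected in every run, so that mean would be neither reported nor tested. This stands for extreme values. It does not stand for moderate ones near 5 SD, which the check often misses.

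Second, a stable chronic abnormality largely cancels in a before-after comparison. That helps the paired tests. Data analysis does not say that the between-group test uses change, so the protection is partial.

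Third, the specialist clause could be used to keep such patients out. The protocol does not say contraindications to what, so this is possible, but it would rest on unwritten individual judgement. An uninformative blood count is not ordinarily a contraindication.

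Fourth, broad eligibility is legitimate in a randomised trial, and an analysis plan not shown may adjust for these conditions. That is fair, and it is why the point concerns efficiency and not validity.

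A reader might go further and infer that one or two such patients can swamp an arm or manufacture a treatment effect. The documents do not support that. t-test power falls to 8% or below only when one patient at 10 SD, or two at 5 SD or more, are all placed in the treated arm. With two forced into one arm and no true effect, the t test does reject in 6% to 9% of trials, but averaged over random placement the error rate stays at about 5% or lower.

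**Conclusion.** The mismatch between eligibility and endpoints is real, and its cost is moderate. Under random placement at 5 SD, one or two atypical patients remove about 19 or 30 percentage points of t-test power (79 − 60, 79 − 49) and about 4 or 8 points of Mann-Whitney power (76 − 72, 76 − 68). The loss therefore depends heavily on which test the normality check selects.

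The result rests on assumed numbers of atypical patients, assumed distances, an upward direction and normal data otherwise. The protocol supplies none of these, so the figures are a range of plausible consequences and not a forecast. Nor should it be inferred that blood disease is wholly unaddressed, since coagulopathy is already a bar to entry. The change is worth making because it is cheap. Leaving the list as it is would not invalidate the comparison.

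**What to change.** Before enrolment, add explicit items to the Non-inclusion criteria, assessed before randomisation from the medical and drug history already taken:

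- haematological malignancy, or recent cytotoxic chemotherapy;
- recent transfusion;
- known active autoimmune or chronic inflammatory disease;
- receipt of an IL-6-pathway inhibitor before the baseline sample.

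The protocol gives no basis for particular time windows, so the investigators should set them. If the sponsor prefers a broad population, the protocol should say so, and the analysis should stratify or adjust for these conditions and for the baseline value, or use ranks or log-transformed values throughout.

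The cost is one amendment, a few otherwise eligible patients and slightly narrower generalisability. The items define entry only and restrict no treatment afterwards. For the same reason they do not deal with values altered by drugs started after baseline, for which the daily drug record is the available source.

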***Exclusion criteria***

- Transfer of patients to the intensive care unit

- Death
- Unwillingness to continue participating in the study

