## **Data analysis**

The data will be analyzed by SPSS software version 25. After examining the normality distribution of variables using Kolmogorov-Smirnov test, quantitative normal variables will be reported as mean $\pm$ standard deviation, quantitative non-normal variables will be reported as median IQR, and qualitative variables as number (percentage). Independent T Test and Mann Whitney test will be used to compare the mean of variables between two groups. Paired T test or Wilcoxon test will be used to analyses within groups means. P-Value <0.05 will be considered as statistically significant. If the patient refuses to continue the study for any reason, statistical methods (Intention-to-treat analysis) will be performed.

1. STEPS, W., *Section 3: guide to physical measurements (Step 2)*, 2008, Geneva.

[figure not shown]

**Figure 1:** Study Process Flow chart

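### ICU transfer, death and unwillingness to continue are exclusions after randomisation, so the biomarker comparison may be a selected one; for refusers the list also conflicts with the intention-to-treat statement

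*Protocol*

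**What the plan says.** Under Study eligibility, patients who may not enter have their own list, headed "Non-inclusion criteria" (pregnancy, low IgA, coagulopathy and so on). A further list, Exclusion criteria, has three items: "Transfer of patients to the intensive care unit", death, and "Unwillingness to continue participating in the study".

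Four other statements bear on the same patients:

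- Study Design & randomization: "Patients will be followed for 14 days", with 24 patients per arm.
- Clinical, Para clinical and dietary intake assessments: blood markers are measured "at the baseline and by the end of week-2". Patients discharged early are still followed and given their drink.
- The same section, on refusers: "If the patient refuses to continue the study for any reason, blood sample will be drawn on the same day". It also says that "mortality rate will be recorded on a daily basis".
- Data analysis: "If the patient refuses to continue the study for any reason, statistical methods (Intention-to-treat analysis) will be performed". This is the protocol's only mention of intention-to-treat.

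**The concern.** A patient cannot die in the study, or become unwilling to continue in it, before joining it. With baseline ineligibility listed elsewhere, the Exclusion criteria can only describe removal of patients who have already been randomised.

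Two of the three events are not neutral losses. The Backgrounds and Objectives section argues that the juice may restrain the inflammatory progression that leads to severe disease and organ failure. ICU transfer and death are the clinical end of that progression. Selecting patients on them means selecting on something the treatment may alter. If the juice helps, placebo may lose more of its sickest patients and the benefit shrinks. If it harms, the juice arm may lose more and the harm shrinks. Chance imbalance between arms of 24 can act in either direction.

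The trial's primary objective is the effect on inflammatory biomarkers and CBC, so this affects its main result. A blood sample not taken from an ICU survivor at week 2 cannot be recovered at analysis.

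**Working it through.** **1. The passages side by side**

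| Event | Exclusion criteria | Sampling provision | Analysis provision |
|---|---|---|---|
| Refusal | excluded | same-day blood sample | intention-to-treat |
| ICU transfer | excluded | none specific | none |
| Death | excluded | week-2 sample impossible | none |

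The first row is a conflict between texts. In the other two rows the intention-to-treat sentence is silent, because it is triggered only by refusal. The conflict there is with the intention-to-treat principle.

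**2. Is there a figure to reproduce?** No. The protocol gives no event rate, effect size, SD or dropout rate. The only sum, 24 + 24 = 48, agrees. All that follows is illustration under stated assumptions.

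**3. Model.** The marker has SD 1, and lower is better. Latent severity has correlation *r* with the marker, and a patient is removed when severity exceeds a threshold *c*. If a fraction *e* of placebo is removed, *c* = z(1 - *e*). Let *h(x)* = φ(*x*)/Φ(*x*). Then:

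- retained placebo mean = -*r* *h(c)*
- retained juice mean = *d* - *r* *h(c - s)*, where *d* is the true effect (negative) and *s* is the shift in severity
- retained difference = *d* - *r*[*h(c - s)* - *h(c)*]

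Assumed ranges: *e* = 10-20%, *d* = -0.3 to -0.5, *r* = 0.5-0.7.

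**4. Identical arms, unequal removal.** Set *d* = 0 and remove the worst 20% of placebo and the worst 10% of juice. *h* at 20% is 0.280/0.80 = 0.350; at 10% it is 0.1755/0.90 = 0.195. The spurious difference is *r* × (0.350 - 0.195) = *r* × 0.155.

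- *r* = 0.5: 0.08 SD
- *r* = 0.7: 0.11 SD

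This counts against the juice, and the sign reverses if the juice arm loses more. With 20% removed from both identical arms the difference is 0.

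**5. True benefit, severity shifting in proportion to the correlation** (*s* = *rd*):

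- Smallest attenuation: *e* = 10%, *d* = -0.5, *r* = 0.5. *h(c)* = 0.195, *h(c - s)* = 0.132. Difference = -0.5 + 0.5 × 0.063 = -0.468, which is 6% smaller.
- Largest: *e* = 20%, *d* = -0.3, *r* = 0.7. *h(c)* = 0.350, *h(c - s)* = 0.269. Difference = -0.3 + 0.7 × 0.081 = -0.243, which is 19% smaller.
- At *e* = 20% and *d* = -0.5: -0.45 (*r* = 0.5) and -0.41 (*r* = 0.7).

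**6. True benefit, severity shifting by the full marker effect** (*s* = *d*):

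- Smallest: *e* = 10%, *d* = -0.5, *r* = 0.5. *h(c - s)* = 0.085. Difference = -0.445, 11% smaller.
- Largest: *e* = 20%, *d* = -0.3, *r* = 0.7. *h(c - s)* = 0.238. Difference = -0.222, 26% smaller.

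This version is strong: at *e* = 20% it implies that the juice cuts ICU/death from 20% to about 13% (*d* = -0.3) or 9% (*d* = -0.5).

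**7. Lost numbers.** Each removal is 1/24 = 4.2% of an arm. Going from 24 to 20 per arm moves the difference detectable with 80% power (two-sided t-test at 0.05; sidedness is not stated, so this is assumed) from 0.83 to 0.91 SD. This is secondary to the selection problem.

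**The case against.** The protocol never says whether exclusion means leaving the analysis set or only ending participation. The provisions for refusers point towards keeping them, and missing-data rules may sit in an analysis plan that is not shown. Deaths can have no week-2 marker under any design.

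Much of this stands, and it rules out several stronger readings:

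- *The comparison is made only in patients who did well.* A reader might infer this, but refusal need not mean a poor course. For ICU transfer and death it holds only if exclusion means removal from analysis or if no week-2 value is obtained.
- *The whole list contradicts the intention-to-treat sentence.* The textual conflict covers refusers only.
- *Recording mortality while excluding deaths is a contradiction.* It is not. A death can be recorded and counted by arm while the patient has no week-2 marker. For the same reason harm is not wholly hidden.
- *Unequal removal of 20% and 10% produces 0.16 SD.* That needs removal on the marker itself, a correlation of 1.0 (1.0 × 0.155).

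What does not stand is leaving the matter to the analysis plan. The exclusion rule is written in the protocol. The protocol makes provision for patients discharged early and for refusers but none for ICU survivors, and an analysis plan cannot supply samples that were not drawn.

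**Conclusion.** The point holds. Randomised patients are excluded for post-randomisation events, two of which lie on the pathway under study, and no rule is given for sampling ICU transfers or analysing ICU transfers and deaths. Followed as written, this gives a selected biomarker comparison. Refusers are both excluded and promised an intention-to-treat analysis, so the reader cannot tell whether they count.

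The plausible distortion is modest but not negligible: about 6-19% attenuation of a true effect (11-26% under the stronger severity assumption), or a spurious 0.08-0.11 SD with 20% versus 10% removal. The event risks, effects and correlations are all assumed. The direction depends on which arm loses more patients. It should be corrected before enrolment, because it touches the primary objective and unsampled patients cannot be recovered.

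**What to change.** Reconcile the Exclusion criteria with the assessments and Data analysis sections, so that these patients are no longer excluded from follow-up and analysis:

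1. State that all randomised patients are analysed in the arm assigned.
2. State that patients transferred to ICU, and patients who stop the drink but still consent to follow-up, have the day-14 CRP, ESR, IL-6 and CBC sample.
3. Separate stopping the drink from withdrawing from the study. Patients who withdraw consent to follow-up give no further samples but are counted in their arm; their withdrawal-day sample is used as a stated missing-data input and not silently treated as a week-2 value.
4. Tabulate ICU transfer, death and withdrawal by arm.
5. Pre-state how missing week-2 values after death or ICU transfer are handled. One option is a sensitivity analysis giving those patients the worst rank in the Mann-Whitney test, which the plan already names. It compares a composite of marker and clinical outcome, so it should be labelled as such.

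Whether the drink itself stops at ICU transfer is a separate clinical decision.

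The cost is revised wording, slightly more follow-up and one additional analysis.

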### **Clinical, Para clinical and dietary intake assessments:**

A demographic questionnaire containing information about age, sex, habitat, education, occupation etc., will be taken from patients. Medical history and medications/supplements history will also be asked of the patient or his companion.

Height, weight and waist to hip ratio (WHR) will be measured by standard methods [1] as well as the body mass index (division of weight in kilograms to the height in meters squared).

For the purpose of evaluating detailed information about nutrient intake and the food pattern, a 24-hour dietary recall for 3 days (including a weekend day) will be taken by a well-trained interviewer. Dietary intakes will be entered into Nutritionist IV software for further analysis.

10 cc blood samples will be obtained after 12 hour overnight fasting to measure complete blood count (CBC) and inflammatory indices including CRP, ESR & IL-6, at the baseline and by the end of week-2. In the case of patient discharge earlier than scheduled, they will be followed up after discharge and receive pomegranate juice or placebo. The length of hospital stay, disease complications, drug and prescription dosing and mortality rate will be recorded on a daily basis. If the patient refuses to continue the study for any reason, blood sample will be drawn on the same day.

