
pathway through the inhibitory effects of conjugated terpenes on PPAR factors is the other protective mechanisms [15, 20]. As far as our knowledge goes, this work is the first study which examines the anti-inflammatory effects of whole pomegranate juice on disease progression in covid-19 patients.

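### ICU transfer and death are post-randomisation exclusion criteria with no stated analysis rule; if exclusion means removal from analysis, patients are dropped by outcome and the comparison between arms can be biased

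*Protocol*

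**What the plan says.** The protocol separates criteria that bar entry (Non-inclusion criteria) from a second list headed Exclusion criteria. The second list has three items: "Transfer of patients to the intensive care unit", death, and unwillingness to go on with the study. All three can occur only after a patient has joined, so the list acts after randomisation.

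The section on clinical, paraclinical and dietary assessments says: "The length of hospital stay, disease complications, drug and prescription dosing and mortality rate will be recorded on a daily basis". The same section provides an early sample for one kind of incomplete follow-up: "If the patient refuses to continue the study for any reason, blood sample will be drawn on the same day". Data analysis uses the same trigger: "If the patient refuses to continue the study for any reason, statistical methods (Intention-to-treat analysis) will be performed". Neither sentence mentions ICU transfer or death.

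The primary objective is "To assess of the effect of Punica granatum juice on inflammatory biomarkers and CBC in patients with Covid-19". The four secondary objectives cover IL-6, ESR, CRP and, last, "To assess and compare the mean or median of CBC parameters before and after the intervention and between the intervention group with placebo". None uses a clinical outcome. The closing sentence of the background, however, says that the study "examines the anti-inflammatory effects of whole pomegranate juice on disease progression in covid-19 patients".

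The design is 24 patients per arm, 48 in all, followed for 14 days. The protocol gives no expected rate of ICU transfer or death.

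**The concern.** ICU transfer and death are the plainest signs that COVID-19 has progressed, and treatment could affect both. A rule that excludes patients on these events after randomisation selects on outcome. If the arms differ in how many patients they lose this way, by effect or by chance, the remaining patients are no longer comparable. The arm that lost more of its sickest patients then looks better on inflammatory markers and on length of stay.

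The primary objective is exposed first. Week-2 CRP, ESR, IL-6 and blood counts would come from patients who stayed out of ICU and survived. A favourable biomarker result could be reported for an arm that had more ICU transfers or deaths, and no objective would bring those events into view.

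**Working it through.** **Setting the sections side by side**

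| Event after randomisation | On the exclusion list | Early blood sample stated | Intention-to-treat stated |
|---|---|---|---|
| Refusal to continue | yes | yes | yes |
| ICU transfer | yes | no | no |
| Death | yes | no (not possible) | no |

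Three events share one list, and only one has a retention rule. The text supports two readings. In the first, exclusion ends participation and the data stay in. In the second, the patient leaves the analysis. Bias arises under the second. It can also arise under the first if these patients have no week-2 marker value and nothing says how that is handled.

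**Size of the bias under the removal reading**

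There is no figure in the protocol to reproduce. The inputs below are assumptions, apart from 24 per arm.

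- Number removed: at event rates of 10% to 25%, 48 × 0.10 = 4.8 to 48 × 0.25 = 12, so about 5 to 12 of 48 patients.
- Let severity be standard normal in both arms, with no treatment effect on the marker, and remove the sickest share p. The mean severity of those left is −φ(q)/(1−p), where q is the (1−p) quantile.
  - p = 0.25: q = 0.674, φ(q) = 0.318, mean = −0.318/0.75 = −0.424 SD.
  - p = 0.10: q = 1.282, φ(q) = 0.1755, mean = −0.1755/0.90 = −0.195 SD.
  - Difference: −0.424 − (−0.195) = −0.229 SD, favouring the arm that lost more.
- Multiply by the correlation between severity and the marker: 1.0 gives 0.23 SD; 0.5 gives 0.229 × 0.5 = 0.11 SD.
- If both arms lose the same share, the two shifts cancel. The bias needs unequal losses.

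For scale, 24 per arm detects (1.960 + 0.842) × √(2/24) = 0.81 SD with 80% power at two-sided 5%. The illustrative bias is therefore 0.11/0.81 = 14% to 0.23/0.81 = 28% of the detectable difference.

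**What the clinical events could show if all 48 are kept**

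The 95% half-width for a risk difference, with the same rate p in both arms, is 1.96 × √(2p(1−p)/24).

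- p = 0.10: 1.96 × √0.0075 = 0.170.
- p = 0.15: 1.96 × √0.010625 = 0.202.
- p = 0.25: 1.96 × √0.015625 = 0.245.

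By the usual normal approximation, power at 24 per arm to detect a halving of the event rate is 9.5% (10% vs 5%), 15.9% (20% vs 10%), 23.3% (30% vs 15%) and 32.3% (40% vs 20%). These outcomes can describe what happened to the patients. They cannot support an efficacy claim.

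**The case against.** The strongest reply is that exclusion here need not mean deletion. Refusal is on the same list, yet refusers get a final sample and intention-to-treat handling, so the protocol's own usage suggests the end of participation. Recording mortality every day would be pointless if deaths were discarded. This stands in part: removal is one reading and not an established fact. But the same comparison shows that the protocol wrote a retention rule for one listed event and none for the other two, so the ambiguity remains.

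A reader might go further and infer that the trial cannot answer its stated question about disease progression, and that recorded mortality must be zero by construction. The document does not support either. Progression appears as the subject of the work only in one background sentence. The formal objectives are biomarkers and blood counts, and the planned samples address them. ICU transfers and deaths are necessarily known, because they trigger the exclusion, so they can be counted by arm. Nor is length of stay known only for patients who did not deteriorate: it is recorded daily, and a patient who worsens without ICU transfer or death is not excluded.

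It is also fair to say that recording clinical data without a matching objective is ordinary practice, and that its tabulation may sit in a statistical analysis plan that was not available. Neither point removes the concern, which is about a rule the protocol itself states. Finally, the bias figures rest on assumed rates, and the upper one needs removal of exactly the sickest patients and a perfect correlation.

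**Conclusion.** The concern holds as a conflict within the protocol that needs resolving. The Exclusion criteria, the daily recording of clinical events, and the refusal-only sample and intention-to-treat sentences do not fit together, and the meaning of exclusion is left open. If it means removal, patients are dropped by outcome, and the bias favours the arm with more ICU transfers or deaths. The illustrative size is 0.11 to 0.23 SD for removal of the sickest 25% versus 10%, with severity-marker correlations of 0.5 to 1.0. Those rates and correlations are assumptions, and equal losses in both arms would give no such difference. The mismatch between the background sentence on progression and the biomarker objectives is a lesser matter of wording.

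**What to change.** Reconcile the three sections in one short amendment:

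- State that ICU transfer and death are outcomes, that they do not remove a patient from analysis, and that all 48 randomised patients are analysed in their assigned arm.
- Extend the intention-to-treat sentence in Data analysis to ICU transfer and death, and say how the biomarker comparison treats a patient with no week-2 value because of either event.
- Add descriptive secondary outcomes by arm, with no confirmatory claim: ICU transfer or death by day 14 (counts and risk difference with 95% CI), complications, and length of stay. With about 24 × 0.10 = 2.4 events per arm at a 10% rate, choose an interval method suited to small counts.
- Record vital and hospital status to day 14 for every randomised patient.
- Align the background sentence on disease progression with the objectives.

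A ranked outcome such as days alive and out of hospital is optional. The fix requires no extra patients and implies no change in clinical care. Most of the data are already recorded daily within the 14-day follow-up; the added work is completing day-14 status for patients moved to ICU. The price is imprecision: intervals of about 17 to 20 percentage points either way at assumed event rates of 10% to 15%.
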